## Abstract

Background: Cardiac implantable electronic device (CIED) placement comes with certain complications. CIED infection is a severe adverse event related to CIED placement. In randomised controlled trials, the preoperative intravenous administration of antibiotics and the adjunctive use of an antibiotic mesh envelope resulted in significant reduction in infections related to cardiac implantable electronic devices. The adjunctive use of taurolidine for this purpose is relatively novel and not considered in the guidelines. The required evidence may consist of a set of clinical studies. Methods: The European TauroPace^TM^ registry (ETPR) prospectively evaluates every consecutive invasive procedure involving any CIED with adjunct TauroPace™ use in the contributing centres. As the estimation of the infection rate needs to be defensible, only interventions registered prior to the procedure will be followed-up. The endpoint is a major cardiac implantable electronic device infection according to the novel CIED infection criteria (1). Secondary endpoints comprise all-cause mortality, complications, adverse events of all grades, and major CIED infections during all follow-up examinations. The follow-up times are three months, twelve months, and eventually 36 months, as acute, subacute, and long-term CIED infections are of interest. Results: As the rate of CIED infections is expected to be very low, this registry is a multicentre, international project that will run for several years. Several reports are planned. The analyses will be included in the case number calculations for future randomised controlled trials. Conclusions: The ETPR will accumulate large case numbers to estimate small event rates more precisely; we intend to follow up on participants for years to reveal possible late effects.

## 1. Introduction

CIED placement is routinely performed to treat cardiac arrhythmias and prevent sudden cardiac death. It is a frequently used therapy with approximately 1.5 million associated procedures per year [1], and usage is increasing [2,3]. Complications occur in around ten percent of patients after CIED placement [4]. Complications comprise lead dislodgement or malfunction, hematoma formation requiring revision, surgical site infections, and other issues [5,6]. The incidence of CIED infections is increasing [2]. Depending on the follow-up period and type of study, infection rates of 1.2–4.2% are reported [6,7,8,9].

Preventative measures proven to be effective include the use of an antibiotic envelope, preoperative intravenous antibiotic administration, and the use of a proper sterile technique. So far, these interventions have succeeded in reducing the above-mentioned infection rates to 0.7% within 12 months and 2.1% within three years [6,8]. Despite this improvement, there is still plenty of room to enhance performance. Antimicrobial surgical site (pocket) rinsing is currently discouraged due to a lack of evidence [1]. 

TauroPace^TM^ (TP, Tauropharm, Bavaria, Germany) is a versatile agent. It is a solution that can be used during any invasive procedure related to CIED placement (e.g., revision with the aim of upgrading, downgrading, or placing any CIED hardware, generator substitution, etc.). Taurolidine is the active agent. During its metabolism, N-methylol groups are released. They display chemicophysical activity against pathogens (i.e., direct destruction and anti-biofilm and anti-surface adherence properties) and the metabolic products/pathogenic constituents (i.e., endo- and exotoxins) released during their destruction [10,11,12].

The European TauroPace^TM^ registry (ETPR) will evaluate the ability of TP to reduce major CIED infections for 3 months, 12 months, and eventually 36 months post-procedure following CIED placement, CIED generator substitution, or upgrade, downgrade, or revision (procedure) in unselected patients (centres that use TP on all procedures) and selected patients (centres that use TP only in patients, who are at a higher anticipated risk of developing a CIED infection according to the PADIT calculator [7]).

The study will serve to record adverse events related to the procedure, the CIED, or the intervention with TP. 

Finally, this investigation will serve as a collection of complications and will be able to prospectively characterize the microbiology of localised CIED pocket infections and bloodstream infections.

## 2. Clinical Evaluation Plan

The ETPR is part of an investigator-initiated clinical development plan. The objective of this clinical development plan is to establish adjunct TP use in CIED procedures. The roadmap to that goal lists several studies to address the different research questions that will have to be answered. These follow the phases set out in the IDEAL framework [13]. 

Idea (IDEAL Stage 1): Taurolidine use is common in locking solutions and recommended in the current guidelines and consensus documents [14,15,16,17,18,19]. Taurolidine solutions are used during lung transplantations [20]. Taurolidine was researched for adjunct use during dental implantation, with a focus on how it affects the buccal microbiome [21,22]. It has shown good results when used during spinal fusion surgery [23]. Taurolidine has been used in different galenic formulations to treat infections in difficult settings [24]. Life-threatening ventricular assist device driveline infections and localised major CIED infections (pocket) were salvaged via debridement using adjunct taurolidine irrigation as a method of last resort [25,26,27,28,29]. 

Development (IDEAL Stage 2a): The physicians involved developed the routine use of adjunct TP during CIED placement and elaborated the standard operating procedure outlined below and on the ETPR website (www.etpr.eu; accessed on 1 June 2023). One manufacturer conducted the preclinical testing and obtained the “Conformité Européenne” for a taurolidine solution: TauroPace™. The investigator-initiated ETPR recording adjunct TP use during CIED procedures follows consecutive cases from multiple centres in a prospective manner [Figure 1]. As the estimation of the infection rate needs to be defensible, only interventions registered prior to the procedure will be followed-up. As the rate of CIED infections is expected to be very low, this registry is a multicentric, international endeavour that will run for several years (ETPR plans to include 2300 procedures and to run until 2030; this depends on the number of centres willing to participate and the annual rate of CIED procedures with adjunct TP use in these centres). Four reports are planned. Analyses will inform the case number calculations for the future studies outlined in Stage 3. The positive reporting of safety will improve the manufacturer’s post-marketing surveillance of safety issues that might otherwise be reported by employing physicians only in clinically relevant cases.

Exploration (IDEAL Stage 2b): A study researching the impact of adjunct TP use against a retrospective control gives a first impression of major CIED infection rates with and without TP (ClinicalTrials.gov Identifier: NCT05576194). These rates may be compared with comparative effectiveness measures from randomised controlled trials (RCTs) of other interventions used for the same purpose. The results could be used for a case number calculation for the planning of future studies. A case–control study of CIED extraction will investigate the reasons for CIED removal. Controls with similar risk factors for CIED infection undergoing CIED placement will be matched to the cases eligible for CIED hardware removal in the event of CIED infection. This is the only study with enough CIED infections to allow multivariable modelling of causation. Its results could guide the participant selection of an initial RCT in selected patients and the case number calculation of an ultimate RCT in unselected patients. 

Assessment (IDEAL Stage 3). Treatment guidelines may mention potential infection prevention with taurolidine after a first RCT of TP against the standard of care as defined in the treatment guidelines at that point in time. This may be the FederaL University of Schleswig-Holstein’s CIED Irrigation Trial (FLUSH-IT) with its comparator of no disinfection of the CIED and its components, or the Worldwide Antibiotic Stewardship in CIED Infection Prevention Trial (**WASH-IT**), which compares the intervention with adjunct TP, without preoperative intravenous antibiotic administration versus the standard of care at that point. To keep the size (and cost) of such a project reasonable, participants are selected according to their potential to benefit from the treatment, and the primary endpoint is defined to prove the direct effect. 

Long-term (IDEAL Stage 4). The ETPR begun at stage 2a will accumulate large case numbers to estimate small event rates more precisely; the plan aims to follow up on participants for years afterwards to reveal possible late effects. At the same time, results from the controlled cohort study and a matched case–control study, plus multiple interim analyses of the registry, are needed for an eventual RCT to begin. The prospective registry should therefore continue for the surveillance of established techniques (SOP from www.etpr.eu). 

## 3. Scope

In addition to the scope of generating feasibility data according to the clinical evaluation plan outlined above:

The ETPR should define and develop patient-, CIED- and procedure-specific understandings of factors driving complications related to the placement of CIEDs in Europe.

The ETPR may shape the development of guidance on how to reach and retain the best possible practice in CIED placement in different settings and countries across Europe.

The ETPR will develop and evaluate a set of suitable tools, solutions, and strategies applicable to the placement of different types of CIEDs with the adjunct use of a new medical device containing taurolidine.

The ETPR will build new site capabilities and develop training activities to increase the number of contributing sites and expand the pool of investigators, including investigators from under-represented communities and naïve investigators in geographies where the study infrastructure may be insufficient.

Ultimately, the ETPR will gain planning data related to the feasibility of conducting future RCTs researching the safety, clinical effectiveness, and cost-effectiveness of adjunct TauroPace^TM^ use against current standard of care in patients eligible to undergo any CIED procedure with the placement of any CIED.

## 4. Methods

### 4.1. Design

The study plan was designed by the authors ([name] and [name]) to meet the criteria of a prospective observational study. The observation was initiated in one contributing centre after consent from the review board of the Bavarian state medical chamber (Nr.:19059). With an increasing number of centres using adjunct TP throughout Europe for CIED placement, the initial study plan was redesigned ([name], [name], [name], [name], and [name]) to a multi-centre observational registry (IRB CAU D420/21) and passed the competent independent ethics committees at the respective contributing centres (EC BLAEK mb21038; EC AEKN GRAE133/2022).

### 4.2. Inclusion/Exclusion

The present prospective observational study includes all consecutive patients with adjunct TP use during CIED placement. This may be in unselected patients (centres that use TP in all patients) or in patients with an anticipated risk for CIED infection according to the results of the PADIT calculator [7] (centres that use TP in high-risk patients only). CIED placement procedures include any invasive CIED procedure (i.e., revision, upgrade/downgrade with or without lead placement, or generator substitution) with adjunct TP treatment of all the CIED hardware before, during, and after placement in patients eligible to undergo a CIED placement procedure receiving any CIED (including and not limited to PPM, ICD, CRT-P, CRT-D, S-ICD, and CCM).

Every procedure with TP enters the final analysis. Standard of care comprises inspection, electrocardiogram, laboratory testing, and cardiac ultrasound for placement and a CIED interrogation in the event of generator replacement, upgrade or downgrade revision, and early revision. Additional medical examinations and diagnostics are performed according to medical needs (i.e., computed tomography angiography, vascular ultrasound, Holter electrocardiogram, coronary computed tomography, cardiac magnetic resonance imaging).

An inability to sign the patient informed consent will lead to the patient’s exclusion.

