### 4.5. Data

The registry allows for a full survey. The data model is based on the following data sources: primary center-based data collection e.g., on specific indication criteria and on the indication of the product under investigation (comorbidities). Indication criteria comprise patient-related risk factors (<65 years, male gender, renal impairment, COPD, heart failure, chronic skin disease, malignancy, immunosuppression, oral anticoagulation, dual platelet inhibition, diabetes mellitus, hematoma formation, and previous implant infection) and procedure-related risk factors (procedure duration longer than 59 min, inexperienced operator, revision, generator substitution, abandoned lead, more than two leads placed, temporary pacing, and bulkier/heavier devices: S-ICD, ICD, CRT), which are recorded. 

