## 5. Endpoints

The primary endpoint is major CIED infection during follow-up.

Major CIED infections are defined in the novel CIED infection criteria [1], resulting in [8]: CIED system removal;an invasive CIED procedure (pocket revision without removal);surgical site infection resulting in pocket revision or CIED extraction after systemic antibiotic therapy;chronic antibiotic therapy due to a major CIED infection without an invasive procedure;death.

Secondary endpoints include all-cause mortality, major CIED pocket infection, minor CIED infection, TP-related adverse device effects (ADE), CIED-procedure-related or CIED-hardware-related adverse events (e.g., pain, arrhythmia, hematoma formation that is resolved, pneumothorax that is resolved), and complications (e.g., hematoma formation requiring revision, pericardial effusion requiring drainage, pneumothorax requiring chest tube, events requiring early pocket revision) during all follow-up periods.

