In order to ensure the applicability of the microbial solution containing taurolidine and the recommendations for the intervention of placing a CIED, there is a particular need for follow-up assessments of widespread use, based on the availability of contributing centres and procedures within a project like the ETPR. The proposed disease area represents an unmet public health need—especially due to increasing procedure rates in the European Union area—and, in the event of complications, a significant burden for patients, healthcare systems, and society. The proposed area, the patients to be evaluated, and the associated complications are representative, to allow for a wide implementation in different cultural and geographical distributions in the context of the proposed clinical research on our catalogue of measures, as well as on TP. Regulators, health technology assessment bodies, and payers benefit from better information on health technologies’ benefit–risk profiles across the patient populations for use in clinical practices.

In comparison to studies of similar or different characters, the ETPR is designed to evaluate multiple baseline characteristics related to the patient, the CIED, and the procedure in different healthcare systems across the continent. At the same time, it does not constrain the investigator to recruit according to certain eligibility criteria. Instead, as stated above, the recruitment of all patients/procedures is encouraged. Therefore, in addition to researching the expressed endpoints, the ETPR opens the possibility of acquiring fine-grain data regarding CIED placement rates, comorbidities, and preferred practices in a scientifically underrepresented population.

Some limitations should be considered when interpreting the potential results of the ETPR in the future: the ETPR is a prospective observational open-label study. The participants may be selected according to an anticipated risk for CIED infection as some centres might use the TP adjunct only in high-risk procedures with high-power devices and numerous host-related risk factors. As the risk calculation is undertaken according to the PADIT calculator [7], which has reliably calculated the anticipated risk for CIED infection [41], this should lead to a higher percentage of patients/procedures with an anticipated high risk for CIED infection being enrolled and should therefore support our hypothesis.

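### Procedures done for an existing CIED infection are not kept out of the primary infection rate, and neither the endpoint nor the estimator requires the infection to be new

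*Protocol article*

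**What the plan says.** **Eligibility (protocol article, 4.2).** The registry takes consecutive patients with adjunct TP. On what counts as an index procedure: "CIED placement procedures include any invasive CIED procedure (i.e., revision, upgrade/downgrade with or without lead placement, or generator substitution". The same sentence goes on to require TP treatment of the hardware in patients eligible for a placement procedure and receiving a device. On the analysis set: "Every procedure with TP enters the final analysis". The one exclusion is: "An inability to sign the patient informed consent will lead to the patient’s exclusion". The Discussion (Section 7) says of the registry that "it does not constrain the investigator to recruit according to certain eligibility criteria".

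**Baseline data (4.5).** The recorded patient-related risk factors end with "diabetes mellitus, hematoma formation, and previous implant infection". Infection present at the time of the index procedure is not listed separately.

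**Endpoint (Section 5).** The primary endpoint is major CIED infection during follow-up. One of the listed consequences that make an infection major is "an invasive CIED procedure (pocket revision without removal".

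**Estimand and estimator (Section 6).** The primary estimand is the rate of patients who develop a CIED infection after a TP procedure and before a repeat procedure or death. The estimator divides procedures followed by an infection by registered procedures with enough follow-up or an event.

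**Table 2.** Two rows lead to no follow-up: another or no disinfectant, and no permanent implantation. The table is headed as applying to the first sensitivity estimand.

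**The concern.** The Introduction gives the objective as TP's ability to reduce major CIED infections after a procedure, and Section 6 compares the rate with historical rates used as fixed performance goals. Persistence or recurrence of an infection already present at the index procedure is a different outcome. If such procedures enter, the reported rate mixes prevention with treatment of infection.

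There is also a possible loop. A major infection may lead to a pocket revision. If TP is used, that revision is itself a procedure type admitted by 4.2. The same infection could then end one index case as an endpoint event and start the next.

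The plan expects very few events, so even one or two carried-over infections matter to the comparison with the performance goals. The same rate is meant to inform sample sizes for later randomised trials.

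**Working it through.** **1. Does the text keep such procedures out?**

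- Procedure type: revision is named in 4.2 without restriction by reason.
- Analysis set: all TP procedures.
- Exclusions: consent only.
- Table 2: the no-implantation row would drop extraction-only procedures. It would not drop a pocket revision with the device kept, or an exchange in an infected system. The disinfectant row is irrelevant here.
- Endpoint and estimator: any major infection during follow-up, and any procedure followed by infection. Neither asks whether the infection was absent at index.
- Estimand: its wording implies a new infection.

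The estimand and the estimator therefore do not match on this point, and no stated rule closes the gap.

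**2. The plan's own figure.**

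Inputs from Table 3 and Section 6: 12-month goal p0 = 1.03% (PADIT), assumed true rate p1 = 0.50%, n = 2300, two-sided 95% level (2.5% in the lower tail), target power 80%.

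- Expected events: 2300 × 0.005 = 11.5.
- Critical count c: the largest c with P(X ≤ c | n = 2300, p0 = 1.03%) ≤ 0.025. P(X ≤ 14) = 0.022 and P(X ≤ 15) = 0.038, so c = 14.
- Power: P(X ≤ 14 | p = 0.50%) = 0.816.

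This agrees with the plan's 80%, so the planning figure stands.

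**3. Effect of including infection-driven procedures.**

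Let f be the share of index procedures done for an existing infection and r the proportion of these with a major infection counted within 12 months. The documents give neither, so both are assumptions. The 0.50% is taken to apply to all other procedures.

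p = (1 − f) × 0.005 + f × r

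| f (assumed) | r (assumed) | Such procedures in 2300 | Carried-over events (2300 × f × r) | p | P(X ≤ 14) |
|---|---|---|---|---|---|
| 0 | – | 0 | 0 | 0.500% | 82% |
| 0.1% | 10% | 2.3 | 0.23 | 0.510% | 80% |
| 0.25% | 10% | 5.75 | 0.58 | 0.524% | 77% |
| 0.5% | 10% | 11.5 | 1.15 | 0.548% | 72% |
| 1% | 10% | 23 | 2.3 | 0.595% | 60% |
| 1% | 20% | 23 | 4.6 | 0.695% | 37% |

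Example for f = 1%, r = 20%: 0.99 × 0.005 + 0.01 × 0.20 = 0.00495 + 0.00200 = 0.00695.

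At the low end the loss is about 2 percentage points of power. With one carried-over event it is about 10, and with two to five it is about 20 to 45.

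**The case against.** The strongest reply is that nowhere does the article say that infected patients are enrolled, and several places point the other way.

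- The eligibility sentence is tied to patients eligible for placement and receiving a device, and the Introduction's example is revision aimed at changing or placing hardware. A debridement-only revision does not plainly fit. This stands as an ambiguity. But 4.3 covers any revision, and being eligible for placement is not defined as being free of infection.
- The estimand most naturally means incident infection. That is right as a reading of intent, but the counting rule and the endpoint do not carry it through.
- Section 4.3 is framed as prevention. The salvage sentence in Section 2, that pocket infections "were salvaged via debridement using adjunct taurolidine irrigation as a method of last resort", might lead a reader to infer that such cases are part of this registry. The documents do not support that: the sentence is background on earlier use, and the registry is described separately as recording routine adjunct use.
- The procedure documents and the full protocol are not shown, and either might screen for active infection. This lowers confidence. It does not remove the difficulty, because the article itself says that all TP procedures are analysed.
- The sizes rest on assumed inputs, and small ones do little harm. The planning rate of 0.5% is also stated as a rate in the registry, so it might already allow for such cases. Both points stand.
- Any bias makes superiority over the goals harder to show. This stands too: the flaw cannot by itself create a favourable result.

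**Conclusion.** The concern holds in a limited form. As written, the inclusion rule and analysis set do not keep procedures done for a known or suspected CIED infection out of the primary rate. The endpoint and estimator do not require a new infection, although the estimand's wording suggests one. A persisting infection could be counted against TP as prevention, and a re-intervention for an endpoint infection could open a new index case.

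The direction is against TP and the size is unknown. Under assumed shares of 0.1–1% and assumed persistence or recurrence of 10–20%, the 12-month rate lies at about 0.51–0.70% instead of 0.50%. Power at 2300 procedures against 1.03% is then about 80–37% instead of 82%.

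A reader might go further and infer that infected cases are certainly enrolled, or that they would dominate the rate. The documents support neither. Enrolment is permitted by the wording but not stated, and even the largest scenario above adds 4.6 events to an expected 11.5. This is a worthwhile and cheap improvement to the plan, not a defect that invalidates it.

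**What to change.** 1. Add one yes/no item to the registration that must already precede the procedure: known or suspected CIED infection at index.
2. In 4.2 and Section 6, limit the primary infection rate, and its comparison with the performance goals, to procedures recorded no.
3. Keep procedures recorded yes in the registry for safety, and report their persistence or recurrence rate separately.
4. State that a re-intervention for a primary-endpoint infection does not open a new index case in the primary analysis.

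The cost is one data field, a few lines of text and a small loss from the primary denominator. At the assumed shares of 0.1–1%, that loss is about 2 to 23 of 2300 procedures. Treatment is unaffected. Recording the item before the procedure avoids having to reconstruct infection status after outcomes are known.

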**Procedure (intervention) with adjunct TP:**

For de novo, upgrade/downgrade revision, early revision, or generator exchange and further clarification, please refer to the SOP CIED placement or SOP CIED revision in the Supplementary Materials section of this manuscript and on www.etpr.eu.

*De novo placement:* After the subcutaneous administration of local anaesthesia, the skin is incised. The generator pocket is prepared. After the placement of the sheath, the pocket is rinsed with TP. The first lead is wiped down and the suture sleeve mobilised with a TP-soaked swab. After placement, the fixation sleeve surrounding the lead is moved to its final position by gripping it with a TP-soaked swab. When sutured to the tissue, the lead, sleeve, and suture are irrigated with 5–10 cc of TP. Subsequent lead placements are carried out accordingly. Before connecting the leads to the generator box, the generator is wiped down with or fully immerged in TP. Both the lead and the generator are gripped with a TP-soaked swab when plugging the lead into the port. The torque wrench is immerged in TP before engaging with the set screws. Once all the hardware is in its final position, the pocket is rinsed with the remainders of the TP. The wound is closed. 

For de novo, upgrade/downgrade revision, early revision, or generator exchange of S-ICDs and further clarification, please refer to the SOP S-ICD in the Supplementary Materials section of this manuscript and on www.etpr.eu.

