The confidence level will not be adjusted for multiple checks, as all analyses will be performed, and conclusions will be based on the latest results of the interim analyses or final results only. Times to major CIED infection or to death will be analysed using Kaplan–Meyer curves and cause-specific hazard ratios for the numbers of risk factors related to the patient, the CIED, or the procedure. ADE and complications will be analysed similarly using logistic regression.

The secondary estimand is all-cause mortality after CIED procedures using TP between procedures accessing the pocket. Intercurrent events are handled similarly (see Table S1 in the online supplement).

To facilitate causal inference in future research, the known risk factors for major CIED infection are reported. Their distribution should enable the calculation of propensity scores or more general balancing weights [31]. Such analyses would consider the randomness of historic controls instead of using historic results as performance goals.

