## Figures and Tables

**Figure 1 mps-06-00086-f001:**
[figure not shown]
Enrolment and follow-up of ETPR participants; CIED denotes cardiac implantable electronic device.

**Table 1 mps-06-00086-t001:** Follow-Up Schedule.

Post-Procedure Visits	De Novo (Including Lead Only in Upgrade or Downgrade)	Box Exchange
Hospital discharge	**X**	**X**
1 month	X	
3 months	**X**	**X**
12 months	**X**	**X**
24 months	**X**	**X**
36 months	**X**	**X**

X, clinical routine; **X**, registry follow-up recorded.

**Table 2 mps-06-00086-t002:** Intercurrent events, their handling in the analysis for the first sensitivity estimand, and the rationale. The prevented bias is the bias that would have been incurred without action. The possible bias is a bias that may be incurred by the action. CI = confidence interval, MNAR = missing not at random, MAR = missing at random.

Intercurrent Event	Prevented Bias	Action	Analysis Strategy	Missingness Assumed	Possible Bias
Other or no disinfectant	Upward	No follow-up	Principle stratum	MNAR	Downward
No permanent implantation	Downward	No follow-up	Principle stratum	MNAR	Upward
Conversion to open surgery	Upward	Full follow-up	Treatment policy	--	Upward
Antibiosis for infections not related to CIED	?	Full follow-up	Treatment policy	--	?
Pocket hematoma, septic thrombophlebitis	?	Full follow-up	Treatment policy	--	?
Minor CIED infection	?	Full follow-up	Treatment policy	--	?
Box exchange	Upward	Competing risk	Hybrid	MNAR	Wide CI
System modification	Upward	Competing risk	Hybrid	MNAR	Wide CI
Other intervention touching the CIED pocket	Upward	Competing risk	Hybrid	MNAR	Wide CI
Death	Upward	Competing risk	Hybrid	MNAR	Wide CI
Lost to follow-up for another reason	Upward, narrow CI	Censoring	Treatment policy	MAR	Wide CI

**Table 3 mps-06-00086-t003:** Historic major CIED infection rates and sample sizes N needed to demonstrate superiority over such external fixed performance goals, if the true new rate is 0.5% at 12 months or 0.33% at 3 months. Sample sizes in bold are selected to issue registry reports.

Source	Follow Up (Months)	Historic CIED Infection Rate (Literature)	Hypothetical CIED Infection Rate (ETPR)	N for Approximate 95% Confidence Interval	N for Exact Test with Power 80%
WRAP-IT [8] verum	3	0.45%	0.33%		
WRAP-IT [8] verum	12	0.7%	0.50%	4778	12200
WRAP-IT [8] control	3	0.80%	0.33%	**572**	2000
WRAP-IT [8] control	12	1.2%	0.50%	**391**	**1420**
PADIT [7]	12	1.03%	0.50%	**681**	**2300**
Henrikson [33]	3	1.0%	0.33%	282	1140

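### Table 2 gives no follow-up to registered procedures that end without a permanent implant; these can already be TP-exposed, so safety events and deaths after a failed implant may go uncounted

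*Protocol article*

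**What the plan says.** - **Who is included and analysed.** Section 4.2 states that the study "includes all consecutive patients with adjunct TP use during CIED placement" and that "Every procedure with TP enters the final analysis".
- **Who is followed.** Section 2 (IDEAL Stage 2a) says that "only interventions registered prior to the procedure will be followed-up". The text adds no condition that the implant succeeded.
- **Table 2.** For "No permanent implantation" the action is no follow-up, the strategy is principal stratum and the missingness is assumed not at random. The bias prevented is downward and the possible bias upward. The caption ties the table to the first sensitivity estimand.
- **When TP is first used.** In Section 4.3, for de novo placement, "After the placement of the sheath, the pocket is rinsed with TP"; the first lead is handled afterwards. For exchange, upgrade, downgrade or revision, the pocket is irrigated with TP before the existing generator is mobilised.
- **Safety endpoints.** Section 5 lists TP-related adverse device effects, procedure- and hardware-related adverse events, all-cause mortality, and complications such as "pericardial effusion requiring drainage, pneumothorax requiring chest tube", all over the follow-up periods. Table 1 marks hospital discharge as a recorded registry follow-up.
- **Mortality.** For the secondary estimand, Section 6 says "Intercurrent events are handled similarly" and refers to Table S1, which is not shown.

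**The concern.** The analysis-set sentence and the Table 2 action cannot both be carried out for a registered procedure in which TP was used and no permanent implant resulted. One rule says it is analysed; the other says no follow-up is collected.

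The loss is unlikely to be random with respect to safety. Drained pericardial effusion, pneumothorax with a chest tube and arrhythmia are all named in Section 5, and each is a plausible reason to abandon an implant. If such patients leave observation because of what happened in surgery, the remaining cohort looks safer than the cohort that was exposed.

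Safety is a stated purpose of the registry. Section 1 says it records adverse events of the procedure, the device and TP. Section 8 says it studies the safety of TP. Section 2 expects its safety reporting to strengthen the manufacturer's post-marketing surveillance.

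**Working it through.** The plan states no figure on this point, so the check is a comparison of its rules.

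**Step 1. Can a procedure without a permanent implant be a TP procedure?** Yes. In both procedure types in Section 4.3, TP enters the pocket before any new hardware is placed. A procedure abandoned after that step has been exposed.

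**Step 2. Is it outside the registry anyway?** Not clearly. Section 4.2 speaks of patients receiving a CIED, but it also covers any invasive CIED procedure. Table 2 treats non-implantation as an intercurrent event, which is something that happens to an enrolled procedure, and not as ineligibility.

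**Step 3. What kind of action is no follow-up?** Table 2 uses four actions:
- Censoring and competing risk are analysis instructions. They can apply to one estimand and leave the data intact for others.
- Full follow-up and no follow-up say what is collected. Data that were never collected are missing for every endpoint, whichever estimand the caption names.

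**Step 4. Does the row's rationale extend to safety?** No. The row guards against a downward bias: a patient without hardware can hardly develop a CIED infection, so counting that patient lowers the infection rate. This supports a principal stratum for infection. It gives no reason to stop observing adverse device effects, complications or death.

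**Step 5. Direction and size.** Let f be the share of TP-exposed procedures without a permanent implant, c1 the complication rate among implanted procedures and c0 the rate among the others. The rate in all exposed procedures is (1 − f)·c1 + f·c0. If failed implants contribute nothing, the reported rate is c1, and the understatement is f·(c0 − c1). It is positive whenever c0 exceeds c1.

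The documents give neither f nor c0. The following are assumptions that show only how the formula behaves:
- With f from 0.5% to 5%, the procedures without follow-up number 2300 × 0.005 = 11.5 (about 12) to 2300 × 0.05 = 115.
- With c1 = 10% (Section 1 cites about ten percent for complications after placement) and c0 = 30% (assumed), the understatement is 0.005 × 0.20 = 0.1 percentage point to 0.05 × 0.20 = 1.0 percentage point. This also assumes that every complication in a failed implant is lost, including those during the procedure.

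**The case against.** **The caption limits Table 2 to an infection analysis.** This is true. Section 6 analyses adverse device effects and complications separately, by logistic regression, and states no exclusion. The mortality handling sits in a table that is not shown. Section 7 says that procedure- and hardware-related adverse events will be recorded, without a condition on implant success. A reader might infer that the plan openly removes failed implants from its safety endpoints; it does not say so. What stands is the inference in Step 3: visits that are not made yield no data for any endpoint. Events seen during the procedure may still be captured, but later ones would not be.

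**The exclusion is conservative.** For infection this is correct, since removing patients without hardware raises the rate. It does not carry over to safety.

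**The prior-registration sentence promises nothing to everyone registered.** Strictly, it states a necessary condition for follow-up. The conflict therefore rests on the Section 4.2 analysis sentence.

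**The disinfectant row.** A reader might extend the point to "Other or no disinfectant", which also carries no follow-up. The documents do not support that. Paired with none, other reads most naturally as in place of TP. The row's prevented bias is upward, which fits procedures without TP. Those are not TP procedures, so Section 4.2 is not contradicted. Nor is a material effect on the infection rate shown: at the planned 0.5%, losing one or two infections would take 1/0.005 = 200 to 2/0.005 = 400 dropped procedures, and nothing in the documents suggests such numbers. The row is merely unclear for procedures that combine TP with another agent, a practice that Section 4.3 discourages.

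**Conclusion.** The point holds for the non-implantation row only. Table 2 and the analysis-set sentence in Section 4.2 conflict for registered, TP-exposed procedures without a permanent implant. The likely consequence is selective loss of safety and mortality follow-up, so that the rates of adverse device effects, complications and death may be understated. The conflict can be read directly from the text. The effect on safety is a strong inference that assumes three things: no follow-up means what it says, Table S1 does not reverse it for mortality, and no unseen rule restores safety visits for these patients.

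The size is unknown. The values in Step 5 are illustrations from assumed inputs and should not be cited as estimates of bias. The infection estimand is not criticised.

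**What to change.** - In the Table 2 row for non-implantation, change the action to full follow-up for safety and mortality in every registered procedure in which TP was used. Align Table S1 if needed.
- Analyse adverse device effects, complications and all-cause mortality in all TP-exposed procedures, implanted or not.
- Apply the permanent-implant restriction only in the infection analyses, and say so beside the analysis-set sentence in Section 4.2.
- As a clarification, state how procedures that combine TP with another agent are classed.

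The cost is a change of wording plus the five recorded visits of Table 1 (discharge and 3, 12, 24 and 36 months) for probably few patients. Under the assumed 12 to 115 procedures, that is at most 60 to 575 visits over the life of the registry. The safety figures may look slightly less favourable. The change should be made prospectively, because follow-up that was not collected may not be recoverable.
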